### Data collection

Data from parents will be collected in de-identified form through anonymous, self-administered surveys. Literacy rates in Sri Lanka are very high for both men and women, so we do not expect illiteracy to be a barrier to participation. Data collection will be supervised by staff recruited specifically for this task. These staff will receive training prior to commencement of the baseline data collection which address the contents of the survey and how to provide confidential, safe and appropriate support to participants who seek or request assistance, including for domestic violence or substance misuse, during completion of the survey. Refresher training will be provided to the same team prior to the collection of post intervention data.

All government preschools in the study areas will be involved in the following data collection activities:A baseline survey of mothers and fathers at the beginning of the preschool year (January 2018)A follow up survey of all mothers and fathers at the end of the preschool year (December 2018).

Preschools receiving the intervention will participate in the following additional post intervention data collection activities:Qualitative interviews with key participants including teachers, community members, community development staff and other government sector service providers to determine their satisfaction with the intervention, and any challenges or barriers to its implementation.

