#### Data analysis

The main analysis will be by intention-to-treat. The primary analysis will be a regression model of IPV experienced by mothers within the past 10 months in the intervention group, adjusted for other potential confounders, and correlation of outcomes within preschools using a Generalised Estimating Equations approach. Primary analysis will be a complete case analysis.

Similar analysis will be conducted for secondary outcomes including prevalence of substance misuse in fathers and awareness and uptake of services for IPV and substance misuse. Secondary analysis will use multiple imputation. Sensitivity analysis will be conducted through secondary adjusted analysis accounting for potential confounders. Confounders specified a priori as being potentially associated with the outcome include age, mental health status and socio-economic status.

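### A confounder-adjusted, complete-case primary model would drop mothers whose IPV outcome was observed, through a filter that acts after randomisation

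*Protocol article*

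**What the plan says.** All the governing statements are in the Data analysis section of the Protocol article.

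- Principle: "The main analysis will be by intention-to-treat".
- Primary model: a regression of IPV in mothers, "adjusted for other potential confounders, and correlation of outcomes within preschools using a Generalised Estimating Equations approach".
- Missing data in the primary analysis: "Primary analysis will be a complete case analysis".
- Missing data elsewhere: "Secondary analysis will use multiple imputation".
- Sensitivity analysis: "Sensitivity analysis will be conducted through secondary adjusted analysis accounting for potential confounders".
- Covariates, named directly after that: "Confounders specified a priori as being potentially associated with the outcome include age, mental health status and socio-economic status".

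Other sections fix where the covariates can come from. Under Data collection, "Data from parents will be collected in de-identified form through anonymous, self-administered surveys", once in January and once in December 2018. Ethical considerations says that no identifying data are held and that records cannot be tied to a person. The Conclusion calls the design repeated cross-sectional. Under Other factors to be assessed, mental health is measured by a depression screening scale in the survey. Under Capacity building intervention, training follows the baseline survey and randomisation.

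**The concern.** Taken together, the adjustment and the complete-case rule mean that a mother counts in the primary analysis only if her IPV answer and every covariate in the model are present. Mothers who decline the violence section are a separate matter, since they have no outcome. The mothers at issue here gave the outcome and left something else blank.

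Because the two surveys are unlinked, an individual covariate attached to a December IPV answer can only have been recorded on the December form. Whether it is filled in is therefore settled after randomisation and after training, and could differ between arms. The randomised comparison does not need these covariates to be valid. The rule discards observed primary outcomes and opens a route for selection that a different analysis set would close.

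**Working it through.** **1. The plan's own figure.** Sample size gives 680 × 0.90 = 612 families, 306 per group, a design effect of 1.5, 40% IPV, 80% power, 5% significance and a 15-point difference. I assume a two-sided test and read the difference as 40% versus 25%.

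Effective n = 306 / 1.5 = 204 per group. With p̄ = 0.325:

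power = Φ[(0.15 − 1.96·√(2·0.325·0.675/204)) / √((0.24 + 0.1875)/204)] = Φ[(0.15 − 0.0909)/0.0458] = Φ(1.29) = 90%.

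The difference detectable at 80% power is 13.1 points. The plan's figure is not reproduced exactly, but it errs on the safe side, so there is slack.

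**2. Outcomes lost to blank covariates.** The documents give no item-missing rate, so the rate q per covariate is assumed. With the three named covariates and independent blanks, the share kept is r = (1 − q)³. Power is shown in two ways:

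- (a) The design effect shrinks with the clusters. A value of 1.5 at 18 mothers per preschool (20 × 0.90) implies an intra-class correlation of 0.5/17 = 0.0294, so the design effect is 1 + (18r − 1) × 0.0294.
- (b) The design effect is held at 1.5, which is pessimistic because smaller clusters carry a smaller design effect.

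| Blank per covariate | Outcomes dropped | Kept per group | Power (a) | Power (b) |
|---|---|---|---|---|
| 0% | 0% | 306 | 90% | 90% |
| 1% | 3.0% | 297 | 90% | 89% |
| 2% | 5.9% | 288 | 89% | 88% |
| 5% | 14.3% | 262 | 87% | 85% |
| 10% | 27.1% | 223 | 83% | 79% |

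Using the article's stated intra-class correlation of 0.025 in (a) gives 85% in the last row. Independence makes the loss large: if the same mothers leave all three items blank, 10% per covariate costs 10% of outcomes, not 27.1%.

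**3. When the loss biases the comparison.** Take no true effect and 40% IPV in both arms, with assumed blank rates.

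- Same pattern in both arms (20% of exposed and 5% of unexposed mothers blank): each arm reads 0.40·0.80 / (0.40·0.80 + 0.60·0.95) = 0.32/0.89 = 36.0%. The difference is zero and the odds ratio is 1.
- That pattern in the intervention arm only, with a flat 10% in controls: 36.0% versus 40.0%, a spurious −4.0 points and an odds ratio of 0.84.

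In the second case the overall blank rates are 0.40·0.20 + 0.60·0.05 = 11% and 10%. Comparing total missingness by arm would not reveal the problem.

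With a real effect (25% versus 40%) and the first pattern in both arms, the odds ratio stays at 0.50 while the difference moves from −15.0 to −14.0 points.

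**The case against.** **The primary model may not be meant to be adjusted.** The section describes an adjusted analysis as the sensitivity analysis, and the covariate list follows that sentence rather than the primary model. If the primary model is unadjusted, a blank depression scale removes nobody. This is a fair reading of an inconsistent section, but the sentence that defines the primary model says adjusted. Either way the section needs rewriting.

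**Multiple imputation is planned.** It is, and a complete-case primary analysis with imputation behind it is a common plan. Here, though, imputation is assigned to secondary analysis. It is unclear whether that means a second analysis of the primary outcome or the analysis of the secondary outcomes. On neither reading does it change the primary estimate.

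**Blanks may be few.** Recruitment and Data collection both provide for supervision by trained staff, Ethical considerations offers help on request, and Data management and quality assurance provides for data queries. It would be wrong to describe the forms as completed without supervision. Still, the forms are self-administered, no passage provides for checking them for blanks before they are handed in, and an anonymous respondent cannot be reached afterwards.

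**The wave is not named, and detail may sit in an analysis plan.** That the covariates come from December is inferred from the lack of linkage. The article offers no other source for individual covariates. The point rests on rules that the article does state, not on detail that it omits.

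Two stronger readings are tempting. One is that the trial would be underpowered. The calculation does not support that: at up to 10% blank per covariate, power stays above 80% or, with the design effect held fixed, falls only to 79%. The other is that the result would be biased because abused or depressed mothers leave the scale unfinished. That pattern alone does not bias the odds ratio if it is the same in both arms, and nothing in the documents shows that it would differ.

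**Conclusion.** The point holds as a problem of avoidable selection and inconsistent wording. Followed as written, the plan removes mothers with an observed primary outcome through a filter applied after randomisation, which does not fit the stated intention-to-treat principle.

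The size is unknown. About 3% to 27% of observed outcomes would go if 1% to 10% are blank on each of three covariates, independently, and fewer if blanks cluster within mothers. The power cost is modest. Bias in the odds ratio requires missingness that depends on arm and IPV together. The 4-point example shows what that could do, not what to expect.

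The conclusion rests on taking the primary-model sentence at its word, on reading complete case as covering covariates as well as the outcome, and on the inference that individual covariates come from the December form.

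**What to change.** In Data analysis, define the primary analysis as all mothers with an IPV answer, in their preschool's allocated arm. Use a GEE model with arm and the stratification factor (study area) and no individual December covariates. Arm and area are known for every mother from her preschool, so nobody is lost to a blank item.

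Make the model adjusted for age, mental health and socio-economic status the sensitivity analysis that the section already names. Run it both as complete case and with multiple imputation, and say which analyses the imputation sentence covers.

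Filling blank covariates with a mean or a missing category inside the primary model is a weaker remedy. It would keep the mothers but still adjust for variables measured after randomisation.

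The change is one of wording and needs no new data. The downside is a small possible loss of precision from leaving individual covariates out of the primary model.

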### Recruitment

All parents from participating preschools will be invited to participate in the study. This invitation will be in the form of a written letter and verbal announcement made by the project intervention team. The parents who volunteer to participate will be invited to attend the school after-hours on a designated day to receive additional information and complete the baseline survey under the supervision of the data collection team. Mothers and fathers will be asked to attend on separate days. Two sessions (a weekday and a weekend session) will be offered to each group to allow participants a choice in the time at which they undertake the survey.

Participation is voluntary and any participant can leave the study at any time they wish. If a participant does leave during the duration of the intervention, any data provided by them up to that point will remain part of the study. Only de-identified data are collected. Therefore, the data collection team and data entry officer are unable to identify any participants who remain or withdraw from the study based on the information received.

In the randomly selected preschools that will receive the intervention, all mothers and fathers will be invited to volunteer to receive capacity building and training as part of the intervention. We aim to recruit two mothers and two fathers participating in initial workshops from each preschool. Those who volunteer will be interviewed by the training team (which is distinct from the data collection team) and selected based on their performance in an initial workshop. Mothers and fathers will attend separate workshops on different days. Training will be delivered to mothers and fathers separately on different days.

All teachers from participating preschools will be invited to attend the teacher training and will be included if they consent. All teachers, 10 randomly selected mothers and 10 randomly selected fathers who participated in the training, will be interviewed at the conclusion of the study.

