#### Other factors to be assessed

Factors identified as associated with IPV and substance misuse in previous research include socio-economic status, educational status, age, marital status and mental health. Data on these factors will be collected, including on mothers’ and fathers’ mental health and depression using a locally developed and validated screening tool for depression (the Peradeniya Depression Scale) [15]. We also postulate that family and community functioning, including measures of social cohesion and inclusion, may be associated with the outcomes of interest. These will be assessed through locally adapted indicators and rating scales measuring family and children’s resilience [16].

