#### Ethical considerations

Parents will be invited to participate in the study as part of a family well-being initiative. The full nature of the study, in terms of the emphasis on IPV, will not be divulged to anyone except the mothers participating and those involved in the support intervention, as recommended by the World Health Organisation guidelines for research into violence against women [18]. Parents will not be aware of the IPV (for mothers) or substance misuse (for fathers) content of the study until they attend the school as per their invitation. Mothers and fathers will attend the school at different times and be issued with different participant information sheets that will contain details of IPV (for mothers) and alcohol and drug support services (for fathers) in the local area. Also listed will be the contact details for the Ethical Review Committees and local study coordinators.

Individual consent will be obtained from all participants before any information is collected from them. Information will be collected from parents via anonymous, self-administered surveys. Mothers and fathers will provide different data by completing different surveys (one for all mothers and one for all fathers). For the mothers, a second stage of written consent will occur within the questionnaire, after full disclosure of the nature of the questions on family violence. If women do not wish to continue, they can submit their questionnaire without signing the second stage of consent and without completing the sections on family violence.

Researchers will not be able to link data to a particular individual within any preschool because identifiable data (including name) are not collected. This ensures confidentiality of response. During completion of the surveys by mothers and fathers, a trained survey team member will be available to assist (in a private space) if help is requested either to complete the survey or to access services.

The Institutional Ethical Review Committee, University of Peradeniya, Sri Lanka (2017/EC/17) and the Human Research Ethics Committee, Australian National University (2017/066), have granted approval for the study. Oversight of the study will be through regular reporting to these ethical review committees.

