## Conclusion

This study will develop, implement and evaluate a community capacity building intervention aimed at reducing IPV and alcohol and drug misuse in communities in Sri Lanka. The innovative method of implementation, delivering this training to parents of children utilising preschools and preschool teachers will reach the most vulnerable sections of the community and will provide a sustainable and feasible strategy for scale up of the project. By intervening through these preschools we aim to build capacity within the community to  identify and support high-risk families early enough to arrest the cycle of violence that results in children themselves becoming victims and perpetrators of such violence.

This research will address important gaps in literature documented by other researchers [3] by robust evaluation through repeated cross-sectional surveys in the target population to assess the effectiveness of the intervention. Preschool communities have not previously been target populations when addressing IPV in Sri Lanka. Results will add to the evidence base for future interventions in Sri Lanka and have potential to contribute to national policy.

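### Mental health status is a pre-specified adjustment variable, but the only individual-level score that can be attached to a follow-up IPV record is post-randomisation

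*Protocol article*

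**What the plan says.** The Data analysis section describes the primary analysis as a GEE "regression model of IPV experienced by mothers within the past 10 months in the intervention group, adjusted for other potential confounders". It then says that "Sensitivity analysis will be conducted through secondary adjusted analysis accounting for potential confounders", and continues: "Confounders specified a priori as being potentially associated with the outcome include age, mental health status and socio-economic status". It does not say at which survey round these variables are measured, or whether they enter at individual or preschool level. Secondary outcomes, including fathers' substance misuse, are to be analysed similarly.

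Under Other factors to be assessed, the measure is an individual questionnaire score for mothers and fathers: "mental health and depression using a locally developed and validated screening tool for depression (the Peradeniya Depression Scale"). That section says that mental health has been found associated with IPV and substance misuse. It gives no direction.

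On linkage the article is consistent:
- Data collection: "Data from parents will be collected in de-identified form through anonymous, self-administered surveys".
- Recruitment: "the data collection team and data entry officer are unable to identify any participants who remain or withdraw from the study".
- Ethical considerations: "Researchers will not be able to link data to a particular individual within any preschool because identifiable data (including name) are not collected".
- Conclusion: the evaluation is "robust evaluation through repeated cross-sectional surveys in the target population".

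The baseline survey is in January 2018 and the follow-up survey in December 2018. Training comes after baseline and randomisation.

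**The concern.** A covariate in a randomised comparison is safe when allocation cannot have changed it. A mother's January depression score would qualify, but nothing in the article allows it to be joined to her December record. What remains at individual level is the December score. It is recorded on the same occasion as the outcome and can have been altered by violence during the recall period. The intervention's support and referral activities could also alter it directly.

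Such a variable is not a confounder of the randomised comparison. Conditioning on it can remove part of the effect, or create an apparent effect where there is none. At stake is whether the adjusted estimate answers the intention-to-treat question that the protocol poses. The fathers' models carry the same risk through the fathers' own scores.

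**Working it through.** **Step 1: which score can be used.** The outcome record is the December questionnaire. Records cannot be tied to a person, leavers and stayers cannot be told apart, no linking code is described, and the design is called repeated cross-sectional. An individual January score therefore cannot reach the December record. A preschool mean of the January scores could, because the preschool is known.

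**Step 2: inputs for the size of the effect.** From Sample size: IPV 40%, and a detectable difference of 15 points, read here as 40% versus 25%. Depression rates given IPV and arm are not in the document. Those below are assumptions, chosen to show a range. All results are large-sample values from exact cell probabilities.

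Unadjusted: OR = (0.25/0.75)/(0.40/0.60) = 0.50; difference = -15.0 points.

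**Step 3: depression responds to IPV only (50% with IPV, 20% without, both arms).** Cell = P(IPV status) × P(depression status given IPV status). OR is the cross-product ratio within each depression stratum.

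| Stratum | Intervention: IPV / none | Control: IPV / none | Risks | OR | Difference |
|---|---|---|---|---|---|
| Depressed | 0.125 / 0.150 | 0.200 / 0.120 | 45.5% v 62.5% | 0.50 | -17.0 |
| Not depressed | 0.125 / 0.600 | 0.200 / 0.480 | 17.2% v 29.4% | 0.50 | -12.2 |

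The share depressed over both arms is (0.275 + 0.320)/2 = 0.2975. Standardised difference = 0.2975 × (-17.05) + 0.7025 × (-12.17) = -13.6 points. The OR stays at 0.50.

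With 60% and 15%, the stratum differences are -15.58 and -10.32 and the share depressed is 0.29625. The standardised difference is 0.29625 × (-15.58) + 0.70375 × (-10.32) = -11.9 points, and the OR is again 0.50.

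**Step 4: the intervention also lowers depression directly (control 60%/20%, intervention 45%/15%).**
- Depressed: OR = (0.1125 × 0.120)/(0.1125 × 0.240) = 0.50.
- Not depressed: OR = (0.1375 × 0.480)/(0.6375 × 0.160) = 0.647.
- Logistic model with arm and depression: OR 0.59, standardised difference -10.0 points.

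With the same depression rates and no IPV effect (40% in both arms), the stratum ORs are 1.00 and (0.22 × 0.48)/(0.51 × 0.16) = 1.29. The model gives OR 1.19 and a difference of +3.5 points.

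**Step 5: the intervention raises reported depression (control 50%/20%, intervention 58%/25%).**
- Depressed: OR = (0.145 × 0.120)/(0.1875 × 0.200) = 0.464.
- Not depressed: OR = (0.105 × 0.480)/(0.5625 × 0.200) = 0.448.
- Model: OR 0.45; with no IPV effect, OR 0.91.

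**Step 6: dependence on the model.** The differences in Steps 3 and 4 are standardised from the logistic fit. Fitting an identity-link model directly gives -13.3, -11.5 and -9.3 points in place of -13.6, -11.9 and -10.0. The conclusion is the same.

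**The case against.** The strongest reply has four parts.

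**The list may belong only to the sensitivity analysis.** It directly follows the sentence on that analysis, and the article does not say that the primary model uses the same set. This stands: the text does not settle which estimate is affected. A reader might infer that the primary result is certainly compromised, and the document does not support that. It does describe the primary model as adjusted for potential confounders, so the primary result is not clearly protected either. A distorted sensitivity analysis could also wrongly cast doubt on a sound primary one.

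**Survey round and level are left open, and an analysis plan not shown could fix them.** A reader might infer that the December value is the only one that could ever be used. That holds at individual level only; a January preschool mean is compatible with the text. But the anonymity is fixed in this document, so no later plan can supply an individual baseline value.

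**Bias in the OR is not inevitable.** This stands. Step 3 shows an unchanged OR when the intervention acts on depression only through the occurrence of IPV. The protocol names no effect measure, and a logistic model is a natural choice.

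**The direction is not known.** This also stands. A reader might infer bias towards no effect, or a spurious harm, but Step 5 reverses the direction. The protocol gives an association between mental health and IPV, with no causal direction and no estimate of the intervention's effect on depression.

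**Conclusion.** The point holds in a conditional form. As written, the plan names an adjustment variable whose only available individual-level version is measured after randomisation, alongside the outcome. Either the primary or the sensitivity estimate, depending on how Data analysis is read, then need not estimate the total intention-to-treat effect.

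Against a true OR of 0.50 and difference of -15.0 points, the illustrations give ORs from 0.45 to 0.59. Where depression responds only to IPV or is lowered by the intervention, the difference shrinks to between about -13.6 and -10 points. With no true effect, the ORs are 0.91 and 1.19. These figures rest on assumed depression rates and show what could happen, not what will. That the score is post-randomisation follows from the document alone; the size and sign of any bias do not.

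**What to change.** Remove individual-level follow-up mental health status from the effect models for mothers and fathers, in primary and sensitivity analyses alike. Adjust only for characteristics that the intervention cannot change: age, study area (the randomisation stratum) and stable socio-economic measures such as education. Current income is less safe. Follow-up socio-economic status is also post-randomisation, and the intervention section describes stronger links to officers who oversee livelihood and welfare programmes.

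If baseline imbalance in mental health is a concern, adjust for the preschool mean of the January depression score. Report follow-up depression as an outcome. State in Data analysis which covariates enter the primary model and which enter only the sensitivity analysis, with survey round and level for each.

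The cost is an edit to the covariate list and slightly less covariate adjustment. No new data are needed. The change should be made before outcome data are analysed.
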